Generally, outpatients are less severely ill (33), which may have implications regarding the implementation of INT for patients requiring hospitalization for treatment. To the best of our knowledge, there have been no trials directly comparing IPT to INT; it is therefore not known if both therapy approaches are equally effective or if one program works better for certain patients or is indeed detrimental for others. Important factors which need to be taken into account are the symptom load and severity in patients requiring hospitalization for treatment, the conditions of the treatment unit, in particular fluctuation in the patient population, together with the presence of patients with disturbing behavior (21).

Therefore, we plan to conduct a single-blind, randomized, controlled trial comparing INT, IPT, and CGP in patients with schizophrenia requiring hospitalization for treatment; to assess the efficacy and feasibility of INT as a treatment programme for such patients. The main outcomes for the assessment of efficacy are changes in symptom load and functionality, together with cognitive performance. Outcomes for feasibility are retention, switch rates, and overall therapy attendance.

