## Methods

### Design

We have designed an 8-week, randomized, controlled, assessor-blind, three-parallel-arm trial for patients diagnosed with a schizophrenic psychosis. All patients with the diagnosis of a schizophrenic psychosis (according to the DSM 5 Diagnostic criteria) are eligible to participate. In order to allow the participation of chronic and low-functioning patients, the inclusion criteria were deliberately broad (see Table 1).

**Table 1 T1:** Inclusion and Exclusion criteria.

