**Assessments**							
Demographic data	X	X					
Psychopathology			X	X	X	X	X
Psychosocial functionality			X	X	X	X	X
Neurocognition			X	X	X	X	X
Medication			X	X	X	X	X
Safety				X	X		

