### Statistical Analysis

We calculated our required sample size using G^*^Power 3.1 (51) (ANOVA: Repeated measures, three groups, four measurement points; effect size F = 0.25; < = 0.05; Power = 0.80; number of groups = 3). Based on that calculation, at least 90 participants (30 in each study arm) completing the intervention are required in order to detect small to moderate size differences. Cohen's d (effect size) will be used to compare the percentage of variation in the groups before and after treatment.

All data sets of participants will be analyzed, on an intention to treat basis. Data at baseline, second week and after the intervention, as well as at 6 and 12-months post-intervention will be considered (see Table 3). The demographic and clinical characteristics of the sample will be compared at baseline using an analysis of variance (ANOVA), except for gender and age, which will be assessed using an analysis of covariance (ANCOVA). To compare the overall effect of treatment over time in the three groups, data from the full intent to treat sample will be analyzed using a repeated-measures analysis of variance (ANOVA) with treatment as the intergroup factor and time as the intrasubject factor. *Post-hoc* analyses will be performed using Student's *t*-test for intergroup comparisons. Reported adverse effects and safety-related events will be analyzed separately as will withdrawal from the study or treatment group changes.

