### Participants Switching Groups, Drop-Outs, and Missing Data

Drop-outs will be replaced until the calculated number of participants has completed the intervention; all enrolled participants will be allowed to complete the intervention. Patient switching therapeutic arm will be considered as drop-outs and will be replaced correspondingly; however, they will be allowed to complete the intervention and outcomes will be assessed as scheduled. For all dropouts, an additional intention to treat, and last observation carried forward analysis will be performed.

In contrast to drop-outs the assessment of outcomes and observation of participants switching groups will be continued. Data prior to switching will be analyzed and reported separately in order to avoid bias duplication of results for a particular participant.

The outcomes of those participants who completed the intervention after switching groups will undergo a *post-hoc* analysis with those who completed their treatment intervention without switching. A multivariate analysis of variance (MANOVA) will be performed, taking into account the switch of intervention together with outcomes measured pre- and post-intervention; i.e., ignoring the outcomes at week two for those not switching intervention arm. Groups for analysis will be constructed according to the number of participants actually switching interventions: the effect of the four first sessions will be categorized according to the change and included in the analysis.

If a participant withdraws from the study, his data will be anonymized, and his name will be deleted permanently from the study.

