Lower functioning patients with low functioning, including those with chronic schizophrenia, seem to benefit from higher frequency psychotherapy (21, 68). We, therefore, concluded that two weekly sessions of 90 min would fulfill this demand. Taking into account the usual length of stay in our unit (6 to 8 weeks), together with current guidelines (17–19) we have chosen to offer at least 16 sessions to participants. For methodological reasons it was not possible to condense both therapeutic interventions to this number of sessions, therefore IPT, INT and CGP have been adapted to 20 sessions programs, respecting the specifications of the treatment manuals.

We considered this to be compatible with the average length of stay in our unit, since some patients remain in treatment for more than 8 weeks. Participants are also encouraged to continue participation after discharge. Although we consider that the completion of a treatment programme to be an important factor determining response, evidence suggests that response is not associated with treatment duration and number of sessions (10).

There is reason to believe that the three treatment arms will differ from one another due to top-down and integration effects on multiple domains. In respect of social- and neuro-cognition, we expect INT and IPT to outperform CGP (36, 69). Nevertheless, we cannot rule out that CGP may also lead to improvements in neuro-cognitive abilities, in particular MCCB domains tested on the computer due to learning and practice effects (12, 70). We expect INT participants to achieve a higher psychosocial performance than CGP, but similar to those of IPT. Although INT and IPT have common roots, applying similar technics for social cognition (23, 27, 37), we expect INT to deliver better outcomes due to its higher complexity and integrative approach (see Table 5).

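### Safety is scheduled only at week 2 and post-treatment, so harm during follow-up and harm in participants who leave without switching is not systematically elicited

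*Protocol article*

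**What the plan says.** On the analysis of harm, the Statistical Analysis section states: "Reported adverse effects and safety-related events will be analyzed separately". The same sentence gives withdrawal from the study and changes of treatment group the same separate treatment. It sets no time limit on the events.

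On collection, the Safety row of Table 3 has two marks, at t2 and t3. The rows for psychopathology, psychosocial functionality, neurocognition and medication each have five, at t1 to t5. The analysis uses the same span: "Data at baseline, second week and after the intervention, as well as at 6 and 12-months post-intervention will be considered".

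On leavers, the section on switching, drop-outs and missing data says: "In contrast to drop-outs the assessment of outcomes and observation of participants switching groups will be continued". It also says that drop-outs are replaced until the target number has completed.

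On why harm is of interest, the Background says it is unknown "if one program works better for certain patients or is indeed detrimental for others". The stated aim, in the next paragraph, is "to assess the efficacy and feasibility of INT as a treatment programme for such patients". The Discussion gives possible detriment as a reason for allowing the switch, and regards two weeks, or four sessions, as long enough to judge whether a therapy is safe.

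**The concern.** At two visits that take place anyway, every assessment running from t1 onwards is marked and Safety is not. The Recruitment section describes patients with frequent or long hospitalisations, so readmission or deterioration in the follow-up year is foreseeable. The Discussion adds: "Participants are also encouraged to continue participation after discharge". Some contact with a programme may therefore continue outside the ward.

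The second gap concerns who supplies the safety data. The post-treatment reading belongs to people who reached the end of treatment. If observation stops for those who leave without switching, the people most likely to have found a programme harmful are the least likely to be asked about it. An arm comparison built mainly on those who stayed is selective, and the document itself treats possible detriment as an open question.

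**Working it through.** The plan gives no figure to reproduce. The check is a reading of Table 3 against the text, with one piece of arithmetic.

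**Step 1: what t1 to t5 mean.** Table 3 does not attach calendar times to these labels. The Abstract and the Statistical Analysis section name five times: baseline, week 2, post-treatment, 6 months and 12 months. The outcome rows have five marks, t1 to t5. The Switch mark stands at t2, and the switch is allowed after two weeks. So t2 is week 2, t3 is post-treatment, and t4 and t5 are 6 and 12 months.

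**Step 2: the rows side by side.**

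| Row in Table 3 | t1 | t2 | t3 | t4 | t5 |
|---|---|---|---|---|---|
| Psychopathology, functioning, neurocognition, medication | X | X | X | X | X |
| Safety | – | X | X | – | – |

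Safety is marked at 2 of 5 points. Its absence at t1 is natural, since t1 is the baseline. Its absence at t4 and t5 is the mismatch.

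**Step 3: share of planned time without a scheduled safety assessment.**
- Treatment length: the Design section says "We have designed an 8-week, randomized, controlled, assessor-blind, three-parallel-arm trial". This agrees with 16 sessions ÷ 2 per week = 8 weeks. The full programme is 20 sessions ÷ 2 = 10 weeks.
- Follow-up: 12 months after treatment, taken as 52 weeks.
- With 8 weeks of treatment: 52 / (8 + 52) = 52/60 = 86.7%.
- With 10 weeks of treatment: 52 / (10 + 52) = 52/62 = 83.9%.

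So roughly 84% to 87% of the planned time lies after the last scheduled safety reading. This is a share of calendar time and not a share of risk.

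**Step 4: who has a scheduled safety reading.**
- Completer without a switch: t2 and t3.
- Switcher: t2, before the change, and t3, because observation continues.
- Leaves without switching before week 2: none.
- Leaves without switching between week 2 and t3: t2 only, so nothing scheduled covers the period in which they left.

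The last two rows follow from the contrast that the article draws between switchers and drop-outs. It does not say outright that drop-outs are no longer assessed.

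**Step 5: does the week-2 reading answer the question alone?** The Interventions and Therapists section says that complexity and emotional demands rise from one INT module to the next. For a participant who begins with the first block, week 2 comes before the more demanding modules. This does not hold for everyone, because the Discussion lets participants join at later blocks.

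**Step 6: which arm would be affected more?** Table 5 gives INT the highest rating for drop-out or switching, in one combined row, and gives CGP the highest rating for completion. The Expected Outcomes text first expects similar retention in all arms, and then slightly higher retention for IPT, followed by INT and then CGP. Table and text point in different directions, so no direction of bias can be derived.

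**The case against.** The strongest reply is that harm is analysed. The Statistical Analysis section covers reported adverse effects without a cut-off date and also analyses withdrawals and group changes. A reader might infer from Table 3 that late harm, or harm that drives a patient out, is left out of account. The document does not support that: each departure is itself an analysed event, and an event reported after t3 is not excluded. This part of the objection stands. What remains is that volunteered reports are not the same as asking at a fixed visit, and that the article does not tie a departure to harm as its reason.

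A second reply is that psychopathology and functioning are rated at t4 and t5, so lasting deterioration would show there. This is also right, and it rules out saying that follow-up contains no information on harm. The scales describe the patient around the visit, however. A readmission that has resolved before the 6-month visit can be missed.

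Third, detriment belongs to the rationale, while the stated aim is efficacy and feasibility. That is so, and it keeps the point modest. Fourth, the two readings fall during and at the end of exposure, and eliciting harm for a year after a short psychological programme is partly a design preference. That is fair too. The case for the change is that the visits exist already.

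Finally, the full protocol may describe how events are collected between visits. Its absence from the article is not a finding. The point rests on the schedule that the article does fix.

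**Conclusion.** The point holds as a low-cost improvement. As scheduled, harm is actively sought at 2 of 5 assessment points, and about 84% to 87% of planned time follows the last of them. Participants who leave without switching have at most the week-2 reading. The scheduled safety comparison therefore rests mainly on those who stayed to t3.

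This depends on three assumptions: that t1 to t5 match the five named times in order, that 12 months is 52 weeks counted from the end of treatment, and that the contrast between switchers and drop-outs means observation of the latter ends.

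A reader might go further and conclude that INT would appear safer than it is. The documents do not support this. The Table 5 row behind it merges drop-out with switching, switchers stay under observation, and the Expected Outcomes text places retention lowest in CGP. The data would be selective, but the direction of any bias between arms is uncertain.

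**What to change.** 1. In Table 3, also mark Safety at t4 and t5, with a question on adverse events and psychiatric readmissions since the last visit.
2. When a participant stops, whatever the number of sessions attended, record Safety once together with the reason for leaving. This is needed in addition to item 1, because extra marks at t4 and t5 do not reach people who are no longer seen.
3. Report these data by randomised arm, including those who dropped out.

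The cost is a slightly longer visit at 6 and 12 months, a short form at stopping and a small amendment. No treatment or switching rule changes. Harm that first appears in a leaver after the stopping record would still depend on spontaneous report.

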### Participants Switching Groups, Drop-Outs, and Missing Data

Drop-outs will be replaced until the calculated number of participants has completed the intervention; all enrolled participants will be allowed to complete the intervention. Patient switching therapeutic arm will be considered as drop-outs and will be replaced correspondingly; however, they will be allowed to complete the intervention and outcomes will be assessed as scheduled. For all dropouts, an additional intention to treat, and last observation carried forward analysis will be performed.

In contrast to drop-outs the assessment of outcomes and observation of participants switching groups will be continued. Data prior to switching will be analyzed and reported separately in order to avoid bias duplication of results for a particular participant.

The outcomes of those participants who completed the intervention after switching groups will undergo a *post-hoc* analysis with those who completed their treatment intervention without switching. A multivariate analysis of variance (MANOVA) will be performed, taking into account the switch of intervention together with outcomes measured pre- and post-intervention; i.e., ignoring the outcomes at week two for those not switching intervention arm. Groups for analysis will be constructed according to the number of participants actually switching interventions: the effect of the four first sessions will be categorized according to the change and included in the analysis.

If a participant withdraws from the study, his data will be anonymized, and his name will be deleted permanently from the study.

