## Abstract

**Background:** Schizophrenic psychoses are severe mental disorders. Despite advances in treatment, outcomes are still unsatisfactory. Pharmacological treatments are still limited, in particular regarding improvements in psychosocial functioning and neuro-cognitive impairment. In recent years new psychological therapies have been developed, demonstrating promising results. However, most of these interventions have been designed for and studied in outpatients; their efficacy and feasibility for patients requiring hospitalization is still unknown. Therefore, we have designed a clinical trial to compare a neuro-cognitive (Integrated Neuro-cognitive Treatment INT); a cognitive-behavioral (Integrated Psychological Therapy IPT); and a control (Cogpack CGP) intervention for patients with a schizophrenic psychosis hospitalized for treatment.

**Methods:** In a three-parallel-arm, single-blind, randomized, controlled study, we compare INT, IPT, and CGP. Participants will take part in two weekly sessions of one intervention for at least 16 sessions. If due to randomization, participants are allocated to a treatment arm not suitable for them, they are allowed to switch intervention after four sessions. Based on a sample size calculation, recruitment will continue until 30 participants have completed the intervention for each treatment arm.

**Outcome Measurement:** Primary outcomes are: change in symptom as measured by the Positive and Negative Syndrome Scale (PANSS), change in psychosocial functioning as assessed by the mini ICF-APP and neuro-cognitive performance, assessed by the Matrics Cognitive Consensus Battery (MCCB). Other outcomes of interest are the Brief Symptom Inventory (BSI) and the Health of the Nation Outcome Scales (HoNOS); together with prescribed medication, treatment retention and completion rates. Outcomes will be measured at baseline, 2 weeks into treatment (prior to a potential switch of intervention arm), post-treatment and at 6 and 12-month post-treatment follow-ups.

**Expected Outcomes:** We expect an overall improvement; however, with differences in specific domains for each treatment arm, with those completing INT showing better outcomes than IPT and CGP, respectively. We anticipate that lower functioning participants will drift to CGP and higher functioning participants to INT.

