### Randomization and Switch Procedure

Following baseline assessment, patients will be randomly assigned (1:1:1 fashion) to either IPT or INT (active interventions) or Cogpack (control intervention). We expect six to eight participants in each treatment arm. Through randomization, there is the possibility that some participants will experience difficulties with their assigned treatment group. In such cases, patients will be permitted to switch to another treatment arm after 2 weeks. The sole criterion for switching intervention arm is patient preference due to excessive, respectively insufficient demands. We have chosen not to formulate explicit criteria for switching intervention arm for two reasons; first of all to empower patients in their commitment to therapy; second to prevent bias through the delayed selection of participants.

After participation in a minimum of 16 sessions (60–90 min each) in one treatment arm, the intervention will be completed; follow-up assessments will be carried out at 6 and 12 months. For a Study- Flow diagram (see Table 3 and Figure 1).

**Table 3 T3:** Schedule of enrolment, interventions, and assessments.

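### The target of 90 is secured only to the end of therapy, but the powered ANOVA reaches into follow-up with no allowance for loss, so 80% power is not assured

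*Protocol article*

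**What the plan says.** The Statistical Analysis section gives the sample-size inputs as "ANOVA: Repeated measures, three groups, four measurement points; effect size F = 0.25", with a 5% level (the symbol is garbled in the text) and 80% power. From these it derives that "at least 90 participants (30 in each study arm) completing the intervention are required". The Abstract turns this into the stopping rule: "recruitment will continue until 30 participants have completed the intervention for each treatment arm".

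The section on switching, drop-outs and missing data sets the replacement rule: "Drop-outs will be replaced until the calculated number of participants has completed the intervention". Switchers fall under the same rule: "Patient switching therapeutic arm will be considered as drop-outs and will be replaced correspondingly".

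The Statistical Analysis section lists five assessments for analysis: baseline, week 2, post-intervention, and 6 and 12 months after the intervention. The main analysis is a repeated-measures ANOVA on the full intention-to-treat sample, with treatment as the between-subject factor and time as the within-subject factor. A last-observation-carried-forward (LOCF) analysis is added for drop-outs. The article states no assumed loss between the end of therapy and month 12.

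**The concern.** The unit counted in recruitment is not the unit counted in the power calculation. The calculation assumes 90 people who each supply four measurements. Recruitment delivers 90 people who finished therapy and so have had the chance to supply three. The fourth measurement must come from follow-up, after most patients have been discharged, in a unit that the Recruitment section describes as treating people with frequent or long admissions. Someone who finishes therapy and then misses month 6 or month 12 has met the recruitment target and triggers no replacement.

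This loss is separate from therapy drop-out and from switching, both of which the plan addresses. It would arise even if every arm reached 30 completers and nobody switched. What is at stake is whether the stated 80% applies to the data set that the ANOVA will actually use.

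**Working it through.** **Inputs from the Statistical Analysis section.** f = 0.25, alpha = 0.05, power = 0.80, k = 3 groups, m = 4 measurement points, N = 90. **Not stated:** which effect was powered, the within-person correlation rho, the sphericity correction epsilon, which four of the five visits were counted, and the follow-up loss d. These are assumptions below.

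**Step 1: visits against the recruitment rule.** By completion of the intervention a patient has had baseline, week 2 and post-treatment, which is three visits. Since m = 4, at least 4 − 3 = 1 powered visit lies in follow-up, whichever four were meant.

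**Step 2: which settings reproduce 90?** Power comes from the noncentral F distribution, with N in multiples of 3.

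- Between-group test: lambda = f²·N·m / (1 + (m − 1)·rho), df = 2 and N − 3. With rho = 0.4 and N = 90, lambda = 0.0625 × 90 × 4 / 2.2 = 10.23 and power is 81.0%; the minimum N is 90. With rho = 0.5, lambda = 22.5 / 2.5 = 9.0 and power is 75.5%; the minimum N is 102.
- Group-by-time test, usual effect-size option: lambda = f²·N·m·epsilon / (1 − rho), df = 6·epsilon and 3(N − 3)·epsilon. With epsilon = 1 the minimum N is 30 (rho = 0.5) or 57 (rho = 0). At N = 90, power is above 99.9% or 96.0%.
- Group-by-time test, Cohen effect-size option: lambda = f²·(N − 3)·3·epsilon. With epsilon = 1 the minimum N is 78 (86.7% at 90). With epsilon = 0.8 the minimum N is 90 (lambda = 0.0625 × 87 × 3 × 0.8 = 13.05; power 80.2%).

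So 90 does not follow from the printed inputs alone. Two sets of unstated settings were found that return it as the minimum: the between-group test with rho about 0.40 to 0.41, and the Cohen-option interaction with epsilon about 0.8.

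**Step 3: effect of follow-up loss.** Complete records = 90(1 − d).

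| Test (m = 4) | 90 (d = 0) | 81 (10%) | 72 (20%) | 63 (30%) |
|---|---|---|---|---|
| Between, rho 0.4 (returns 90) | 81.0% | 76.4% | 70.8% | 64.2% |
| Interaction, Cohen option, epsilon 0.8 (returns 90) | 80.2% | 74.9% | 68.6% | 61.2% |
| Between, rho 0.5 | 75.5% | 70.5% | 64.8% | 58.3% |
| Interaction, Cohen option, epsilon 1 | 86.7% | 82.0% | 76.1% | 68.7% |
| Interaction, usual option, rho 0 | 96.0% | 93.7% | 90.1% | 84.9% |
| Interaction, usual option, rho 0.5 | >99.9% | 99.9% | 99.8% | 99.4% |

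In the two rows that return 90 there is almost no reserve: at 87 complete records (three lost) power is 79.6% and 78.6%. In the last two rows power stays at or above 80% until about 37% (rho 0) or 67% (rho 0.5) are lost.

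**The case against.** The strongest reply is that no shortfall has been shown. The article gives no loss rate, no correlation and no test option. Its stated aim of comparing treatment over time reads naturally as the group-by-time interaction, for which 90 leaves a large surplus under the usual settings. At rho 0.5 the between-group test is below 80% before anyone is lost, so attrition would not be the cause there. The rho of 0.4 is back-fitted to return 90. All of this stands. It rules out a stronger reading that a reader might infer, namely that the stated 80% is definitely not reached.

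A reader might also infer that the powered ANOVA needs every visit to month 12. The text does not say so: four points were powered, five visits are listed, and the four are not named. At least one follow-up visit is needed; which one is unknown.

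Nor is it shown that fewer than 90 people will be analysed. The ANOVA is planned on the full intention-to-treat sample, replaced drop-outs and switchers are enrolled on top of the 90, and LOCF is planned as an addition. That relief is limited. Observation of drop-outs is contrasted with that of switchers, which continues, so drop-outs apparently supply no later visits. The Discussion counts switchers as drop-outs in the primary analysis. LOCF is tied to drop-outs, and a therapy completer who misses month 12 is not clearly one.

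Finally, a condensed article may leave missing-data detail to a fuller document. But the count of 90 and the point at which replacement stops are fixed here, and the mismatch lies between those two statements.

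**Conclusion.** The point holds as a gap in assurance, not as a proven shortfall or an arithmetic error. From the text alone, the 90 are counted and replaced only to the end of therapy, the powered design includes at least one later visit, and no loss is allowed for there. Taking the protocol at its word that 90 is the minimum for 80%, fewer records complete at the powered visits give less than 80% in an ANOVA that uses complete records only.

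The size cannot be fixed from the article. For losses of 10% to 30%, it runs from 76% down to 64% (between-group test, rho 0.4) to no material problem (group-by-time test, usual option, rho 0 to 0.5, still 85% or more at 63 records). The loss rates, the correlation, epsilon, the choice of test and the complete-record analysis are all assumptions.

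**What to change.** In the Statistical Analysis section, state which effect was powered, which four of the five visits were counted, the correlation (and any sphericity correction) used, and an assumed follow-up loss. Restate the power for the number expected to have those visits, and say that 30 per arm refers to the post-treatment visit.

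Replace the classical repeated-measures ANOVA, and LOCF as its added analysis, by a likelihood-based mixed model on all available visits of all randomised patients. A completer who misses a follow-up visit then still contributes the earlier ones.

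The cost is rewording, a little analysis work and possibly a less favourable power figure; no additional patients or visits are needed. Should the authors prefer to keep 90 complete records through follow-up, the number of completers would be 90/(1 − d): 100 at 10% loss, 113 at 20% and 129 at 30% (102, 114 and 129 in equal arms).
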